### Radiotherapy quality assurance (QA)

Treatment plans created in the FLASH-capable Eclipse TPS 16.5 system will be imported into the ARIA Oncology Information System (Varian Medical Systems, Palo Alto). As per routine practice, daily machine QA and patient-specific QA will be performed in preparation for FLASH therapy treatments.

Machine QA includes standard daily machine QA (e.g., safety checks, output checks) as well as dose rate verification using the FLASH QA tool. The FLASH QA tool is stand-alone software that analyzes the Pencil Beam Scanning log files associated with FLASH treatment plans to verify that the FLASH-enabled ProBeam is delivering at FLASH dose rates of at least 40 Gy/s.

Patient-specific QA for study participants treated on this study protocol will be performed, for example, using film and/or ion chamber dosimetry. The patient-specific QA program is substantially similar to standard Intensity-Modulated Proton Therapy (IMPT) patient-specific QA. The patient quality assurance procedure determines whether a planar dose calculation is within a clinically acceptable tolerance of a planar dose measurement.

An RT review committee, consisting of an external group of expert radiation oncologists, will perform post-treatment review of FLASH RT plans for every third study participant.

### FLASH therapy

The present clinical study (FAST-02), like the preceding FAST-01 trial, will be carried out at an investigational site with a ProBeam Proton Therapy System (Varian Medical Systems, Palo Alto), an FDA cleared device (K133191), that utilizes a cyclotron to deliver proton radiation, and that has been modified to deliver the proton radiation at a FLASH dose rate.

The treatment plan will be transferred from ARIA to the ProBeam Proton Therapy System console for FLASH RT delivery. Image guidance will be used to verify that the target is in the correct position for treatment.

## Follow-up

A summary of study visits and activities is provided in Table 2. It will be acceptable to carry out remote follow-up visits as an alternative to in-person visits in the event of the study participant’s inability or reluctance to travel as well as for progressive subject disability. In these circumstances, photographs of the treatment site may be taken at home by caregivers, questionnaires may be completed at home as the subject’s clinical status permits, and physical evaluations may be carried out to the extent those are feasible via telehealth. A mobile nurse may also be used for home visits to carry out study activities such as physical assessments and assisting subjects with data collection when in-person visits are not possible. If remote follow-up is not possible, then an effort will be made to collect study data from a review of subject records (e.g., electronic medical records, hospice records, etc.) as available to the investigator.

**Table 2 Tab2:** Schedule of activities

	Treatment Simulation to Treatment Delivery (≤ 10 business days)				Post Treatment Follow-up						
**Event**	Enrollment, baseline (1–2 weeks)	Prep for treat-ment	Prior to treatment delivery (Day 1)	Treatment delivery (Day 1)	After treatment delivery (Day 1)	Day 2 - Day 11 (daily)^1^	Day 2 (± 1 calendar day)	Day 7 (± 2 business days)	Day 15 (± 2 business days)	Month 1 (± 5 business days)	Months 2, 3, 6, 9, 12, then every 6 months
Patient screening (initial inclusion/ exclusion criteria)	X										
Informed consent	X										
Demographics	X										
Disease information	X										
CT-based simulation		X									
Treatment planning		X									
Treatment plan QA		X									
FLASH treatment delivery				X							
Questionnaire for pain flare assessment			X			X					
Questionnaire for overall pain assessment			X					X	X	X	X
Questionnaire for pain assessment at treated sites			X					X	X	X	X
Subject evaluation^2^	X		X					X	X	X	X
Review of pain medication (including steroid medications)			X			X		X	X	X	X
AE evaluation^3^					X		X^4^	X	X	X	X

^1^ Day 2-Day 11 subject evaluation: review of pain medications (including steroid medications) and pain flare assessment will be completed by telephone check-in.

^2^ Includes performance status and physical evaluation with skin photographs.

^3^ All AEs and SAEs will be captured regardless of severity or attribution.

^4^ Day 2 AE check will be carried out through a remote visit.

Outcomes will be evaluated against data collected as part of the baseline evaluation and on the day of treatment (but before start of treatment) as follows:

Subject characteristics: date of birth, sex, ethnicity, race, history of medical comorbidities or genetic or autoimmune disorders, diagnosis date, and prior cancer-directed treatments.Tumor characteristics: histology, anatomic location of the original primary tumor and the anatomic location of treatment site(s), target lesion size, and radiographic appearance of the target (e.g., lytic, sclerotic).Baseline data specific to outcome assessments: performance status, photographs of skin and any physical findings on examination involving the skin or other normal tissue in the planned treatment site(s), and information about treatment for other bone metastases not treated as part of this study.Pain medications (including narcotics, gabapentin class drugs, other non-narcotic analgesics, and steroid medications).

If a study participant leaves the study for any reason before the next scheduled follow-up visit is completed, the investigator will document the reason(s) to the extent known by the investigator. In addition, the investigator will attempt to collect a final assessment of the following: patient-reported pain score (overall and specifically for treated site(s)), use of pain medications (including steroid medications), and AEs, including skin and other normal tissue toxicities.

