## Outcomes

### Toxicity

AEs will be monitored from the start of treatment to the completion of the final study follow-up visit. All AEs will be collected regardless of severity or attribution and will be classified per Common Terminology Criteria for Adverse Events (CTCAE) version 5.0. The outcome of toxicities that are possibly, probably, or definitely attributed by the investigator to FLASH RT will be assessed through AE checks, photographs, and pain flare questionnaires. The AE check on Day 2 will be carried out by remote review. In some circumstances, AE checks during follow-up may be carried out using a combination of remote visits and/or records review.

Photographs of skin at the entry and exit sites of the radiation beam will be captured at AE checks to facilitate grading and attribution of any skin AEs. If the treated area(s) are readily identifiable, the photographs should encompass the entire anatomic region treated with close-up photographs of the skin in each treated area.

Pain flare (transient increase in treated site bone pain following RT treatment) will be assessed at Day 1 (baseline pain prior to treatment) and daily for the first 10 days (Day 2–11) following the treatment day using the methodology of Chow et al. [18]. This patient-reported assessment will collect the following information for each treated site: (1) worst pain over the last 24 hours and (2) patient-reported comparison of this worst pain to the worst pain in the treated site on the day of treatment. Participants’ use of pain medication will be logged.

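### The daily telephone calls on Days 2 to 11 include no general adverse event question, which leaves a nominal 5-day and at worst 10-day gap between scheduled adverse event checks

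*Protocol article*

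**What the plan says.** Toxicity is one of two co-primary objectives (Methods, Objectives). Under Outcomes, Toxicity, "AEs will be monitored from the start of treatment to the completion of the final study follow-up visit", and every AE is to be collected whatever its grade or cause. Toxicities attributed to FLASH "will be assessed through AE checks, photographs, and pain flare questionnaires".

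Table 2 (Follow-up) fixes when this happens in the first days:

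- The AE row is marked in the column "After treatment delivery (Day 1").
- It is marked again at "Day 2 (± 1 calendar day"). Footnote 4 says that the "Day 2 AE check will be carried out through a remote visit", and the Toxicity section agrees: "The AE check on Day 2 will be carried out by remote review".
- The next mark is at "Day 7 (± 2 business days").
- In the daily column for Days 2 to 11 the AE row is blank. Only the pain flare questionnaire and the pain medication review are marked there. Footnote 1 describes the contact in the same terms: "review of pain medications (including steroid medications) and pain flare assessment will be completed by telephone check-in".

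No section sets a minimum interval between AE checks or keeps the Day 2 check off Day 1.

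**The concern.** Staff speak to the participant every day for ten days after treatment, yet the schedule does not require them to ask about anything except pain and analgesics. The Treatment planning section expects that some lung may lie in the field, and Table 1 sets limits for oesophagus and heart as well. Respiratory, oesophageal and skin symptoms are therefore of interest from the start. A mild event that appears and resolves between two checks depends on the participant volunteering it or recalling it days later.

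All grades are in scope, so these events count towards the co-primary outcome. With 10 participants, one participant whose event is missed moves an incidence by 1/10, or 10 percentage points.

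The visit windows can stretch the interval further. The Day 2 check may be brought forward onto the treatment day, where it adds little to the post-delivery evaluation, and the Day 7 check may slip by two business days.

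**Working it through.** The protocol states no figure for the interval between AE checks, so there is none to reproduce. The calculation is a calendar count.

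**Inputs (Table 2)**
- Treatment and first AE evaluation: Day 1.
- Second AE check: Day 2 ± 1 calendar day, so Day 1 to Day 3.
- Third AE check: Day 7 ± 2 business days.
- Assumptions: treatment on a weekday, business days Monday to Friday, no public holiday.

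**Formula:** gap = day number of the latest Day 7 check − day number of the Day 2 check.

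**Latest permitted Day 7 check**

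| Day 1 | Day 7 falls on | + 2 business days | Day number |
|---|---|---|---|
| Monday | Sunday | Tuesday | 9 |
| Tuesday | Monday | Wednesday | 9 |
| Wednesday | Tuesday | Thursday | 9 |
| Thursday | Wednesday | Friday | 9 |
| Friday | Thursday | Monday | 11 |

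**Gap without a required general AE question**

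| Timing of the two checks | Monday to Thursday treatment | Friday treatment |
|---|---|---|
| Both on nominal days | 7 − 2 = 5 | 7 − 2 = 5 |
| Day 2 on Day 3, Day 7 at latest | 9 − 3 = 6 | 11 − 3 = 8 |
| Day 2 nominal, Day 7 at latest | 9 − 2 = 7 | 11 − 2 = 9 |
| Day 2 on Day 1, Day 7 at latest | 9 − 1 = 8 | 11 − 1 = 10 |

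A public holiday on that last Monday would move the Friday case to Day 12, a gap of 12 − 1 = 11 days.

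**Effect of each possible edit**
- Day 2 window changed to 0/+1 calendar day, nothing else: the maximum falls from 8 to 7 days (Monday to Thursday) and from 10 to 9 days (Friday).
- One AE question in each daily call: the gap through Day 11 is 1 day, whatever the windows do.

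The blank AE row in the daily column is therefore the main cause. The Day 2 window contributes one day.

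**Bearing on the pause rule**
The Results section expects enrolment to take 15 months. With even accrual of 10 participants, that is 15/10 = 1.5 months, or about 45 days, per participant. In a 10-day gap about 10/45 ≈ 0.2 further participants would be treated.

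**The case against.** The strongest reply is that the longest interval is a corner case. Ten days needs a Friday treatment, a Day 2 check brought forward to Day 1, and a Day 7 check on its last permitted day. A second check on the day the participant has just been assessed is in window but defeats its evident purpose. This stands, and the 5-day nominal gap should lead any description of the point.

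Three stronger readings are tempting, and the documents do not support them.

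- **That nothing about toxicity is asked for up to ten days.** Pain flare questioning is itself a named means of assessing toxicity and takes place daily. The Toxicity section has AE monitoring running from the start of treatment, so an event volunteered on a call would be recorded. What is missing is a scheduled general question.
- **That a Friday treatment pushes the Day 2 check onto Day 1 because the weekend follows.** The Day 2 window is in calendar days, and the daily calls already fall on that Saturday and Sunday.
- **That the stopping rules are seriously weakened.** Accrual is slow, and the toxicity rule based on grade 3 or higher events needs at least two affected participants. The device rule relies on the dose monitoring system. Any delay is a minor matter.

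It can also be said that the article condenses a fuller protocol, in which a call script may already prompt for AEs. That is possible. However, the article does state the content of the calls, and Table 2 fills the AE row at other time points and leaves it blank here. The point concerns a schedule as stated, and does not rest on an omitted detail.

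**Conclusion.** The point holds as a cheap improvement. Table 2 requires no general AE question between the Day 2 and Day 7 checks, although staff are in daily contact with the participant. The gap is 5 days on nominal timing and 7 or 9 days with only the Day 7 check at its latest. It reaches 8 or 10 days in the worst case, the larger figure in each pair applying to Friday treatment. These figures assume weekday treatment and no public holiday.

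The consequence is late or incomplete capture of short-lived, mostly low-grade AEs for a co-primary outcome in 10 participants. The documents do not allow an estimate of how many events would be lost. Nothing in the schedule is contradictory or miscalculated.

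**What to change.** 1. **Main edit.** In Table 2, mark AE evaluation in the daily column for Days 2 to 11, and add to footnote 1 that each telephone check-in includes one open question about any new or changed symptom. The Day 7 visit stays as it is, with its physical evaluation and skin photographs.
2. **Secondary edit.** Change the Day 2 window to 0/+1 calendar day, so that the check cannot duplicate the Day 1 evaluation. On its own this removes only one day from the maximum gap.

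The cost is one question in a call already being made, one change of window, and somewhat more low-grade AEs to record and attribute. The protocol already asks for those events to be collected.

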## Outcomes

### Toxicity

AEs will be monitored from the start of treatment to the completion of the final study follow-up visit. All AEs will be collected regardless of severity or attribution and will be classified per Common Terminology Criteria for Adverse Events (CTCAE) version 5.0. The outcome of toxicities that are possibly, probably, or definitely attributed by the investigator to FLASH RT will be assessed through AE checks, photographs, and pain flare questionnaires. The AE check on Day 2 will be carried out by remote review. In some circumstances, AE checks during follow-up may be carried out using a combination of remote visits and/or records review.

Photographs of skin at the entry and exit sites of the radiation beam will be captured at AE checks to facilitate grading and attribution of any skin AEs. If the treated area(s) are readily identifiable, the photographs should encompass the entire anatomic region treated with close-up photographs of the skin in each treated area.

Pain flare (transient increase in treated site bone pain following RT treatment) will be assessed at Day 1 (baseline pain prior to treatment) and daily for the first 10 days (Day 2–11) following the treatment day using the methodology of Chow et al. [18]. This patient-reported assessment will collect the following information for each treated site: (1) worst pain over the last 24 hours and (2) patient-reported comparison of this worst pain to the worst pain in the treated site on the day of treatment. Participants’ use of pain medication will be logged.

### Efficacy

Patient-reported overall pain will be collected through the use of the brief pain inventory (BPI) short-form questionnaire. Patient-reported pain for each treated site will be assessed using a four-item subset of the BPI questionnaire [10]. These questionnaires (for overall pain and pain at the treated sites) will be completed on Day 1 (prior to treatment) and on Day 7, Day 15, Month 1, Month 2, Month 3, Month 6, Month 9, Month 12, and every 6 months thereafter. They may be collected using a combination of in person or remote visits and/or, from Day 7 onward, medical records review.

Use of pain medication will be collected and changes in pain medication use will be evaluated between baseline, during each of the first 10 days after treatment, and follow-up visits Day 7, Day 15, Month 1, Month 2, Month 3, Month 6, Month 9, Month 12, and every 6 months thereafter.

### Clinical workflow

The FLASH clinical workflow outcomes are (1) time on the treatment table and (2) occurrence of any device issues. Device issues include, but are not limited to, delays in study treatment related to the investigational device, excluding delays due to subject or facility factors not related to study treatment.

## Stopping rules

Triggering of any one of the following rules will result in a pause of enrollment by the Sponsor, followed by Sponsor and DSMB review of the study data if:

2 out of 6 study participants, or if 3 or more study participants, experience grade 3 or higher toxicity that is possibly, probably, or definitely related to study treatment;1 subject experiences a grade 5 AE, unless probably or definitely related to the underlying disease, complications of subsequent cancer therapies, or extraneous causes; A major device malfunction in dose delivery occurs (as indicated by the dose monitoring system). This includes potential recordable or reportable medical events under the Ohio Department of Health classification.

The DSMB will make recommendations regarding continuation or cessation of enrollment.

## Results

Enrollment for the study is expected to take 15 months. Subjects will be on study prior to their radiation treatment simulation (approximately 1–2 weeks); during their radiation treatment simulation, treatment planning, and delivery (≤ 10 business days); and during post-treatment follow-up (until subject death or lost to follow-up). The study may run from 2.5 years to several years (which covers enrollment, treatment, follow-up, and completion of data analyses).

## Discussion

Bone metastases are a common complication of cancer. The pain associated with bone metastases can have a significant adverse impact on a patient’s quality of life. While other focal modalities are being evaluated as an alternative or supplement to RT, such as magnetic resonance image-guided high-intensity focused ultrasound (the three-armed randomized controlled ‘FURTHER’ trial) [19], external beam RT remains a current standard of care for pain management.

The FAST-02 study is designed to assess the pain relief and toxicities of treatment in patients with painful thoracic bone metastases treated with FLASH RT. It is the first clinical trial evaluating FLASH therapy for this clinical indication and for the treatment in the thorax, and only the third prospective clinical trial to be activated worldwide studying ultra-high dose-rate FLASH RT.

The US Food and Drug Administration (FDA) has authorized the clinical investigation to move forward with FLASH therapy in a study limited to 10 participants. Proton FLASH is a novel treatment strategy, used previously in only one prospective proton clinical trial (FAST-01), and the clinical data generated by this FAST-02 protocol will contribute to the assessment of the safety and efficacy of this treatment modality. Until additional data are generated on the risk of AEs from FLASH, spinal metastases (requiring direct FLASH irradiation of the spinal cord) are not eligible for treatment under this protocol. To spare normal tissue in the region of the treatment, this study will use image-guided setup for the FLASH treatment and a conformal treatment planning technique.

The data acquired in this investigation will provide clinical data to answer the question of whether FLASH therapy is safe and effective in the treatment of thoracic bone metastases. Based on the results of FAST-01, treatment is expected to be effective and well-tolerated. If the results prove to be favorable, this study will support the further exploration of FLASH therapy for broader clinical indications.

## Data Availability

N/A.

## Abbreviations

4DCT: Four-dimensional computed tomography
AE: Adverse event
SAE: Serious adverse event
CCHMC: Cincinnati Children’s Hospital Medical Center
CT: Computed tomography
CTCAE: Common Terminology Criteria for Adverse Events
DSMB: Data safety monitoring board
RT: Radiation therapy
ITV: Internal Target Volume
